#### Process

Number of eligible women who are approached and enrolled into the study per month. (Documentation)Percentage of intervention participants who complete the initial and support sessions. (Documentation at each relevant time point)Percentage of participants in each group who attend the follow-up visit. (Documentation)Percentage of participants for whom weight at 36 weeks’ gestation is available (usually measured as part of a routine hospital appointment).Proportion of participants who record their blood glucose and blood ketones every week. (Documentation from baseline until before delivery)Proportion of participants in the intervention group who self-monitor their weight every week. (Documentation from baseline until before delivery)Proportion of participants in the control group who, after randomisation, follow a reduced-carbohydrate diet (contamination of the control group). (Dietary composition analysis at baseline and follow-up visit—see details below)Proportion of essential elements included in intervention delivery sessions (main and support sessions). (Evaluation of audiorecorded sessions against a checklist)

#### Exploratory outcomes

Further dietary changes: fibre intake, percentage of daily total energy intake from total fat, saturated fat and protein. (Dietary composition analysis at baseline and follow-up visit—see details below)Changes in systolic and diastolic blood pressure from baseline to follow-up.Changes in pregnancy-related outcomes for example, gestational hypertension and pre-eclampsia, requirement for insulin or oral diabetic medication, mode of delivery, induction of labour, gestational age at delivery, birth weight, sex of baby, rates of macrosomia (>4500 g),^43^ large-for-gestational age (>90th percentile) and small-for-gestational age infant (<10th percentile),^43^ neonatal adverse events, for example, neonatal intensive care unit admission, shoulder dystocia/birth trauma, neonatal hypoglycaemia requiring intravenous glucose, neonatal hyper bilirubinaemia requiring phototherapy. (Extraction from medical record following delivery)Change in quality of life from baseline to follow-up.Participant acceptability of the intervention and the materials, overall experience of the intervention, barriers and facilitators of adherence (qualitative interviews).

### Measurements

A schedule of measurements can be found in table 1.

**Table 1 T1:** Schedule of study measurements

		Study period							
	Enrolment	Allocation	Study visits/sessions						Delivery
**Time point**	Baseline=week 0 (<20 weeks’ gestation)	Week 0	Week 2	Week 4	~Week 8	Follow-up visit = ~Week 12 (24–28 weeks’ gestation)	~Week 16	~Week 20	Week 24
**Enrolment:**									
Eligibility screening	X								
Informed consent	X								
Randomisation	X								
Trial arms:									
**RECORD programme**	X	X				X			X
									
+ telephone support			X	X	X	X	X	X	
Usual care	X	X				X			X
									
**Assessments:**									
Demographics	X								
Weight	X					X			
Height	X								
Blood pressure	X					X			
OGTT	X					X			
EQ-5D	X					X			
Self-completed 24-hour dietary recall	X					X			
Fasting plasma insulin	X					X			
HbA1c	X					X			
Self-monitoring of fasting capillary glucose		Twice a week for the study duration 							
Self-monitoring of fasting capillary ketones		Twice a week for the study duration 							
Self-weighing (intervention group)		Once a week for the study duration 							
SAEs									
Maternal and neonatal outcomes									X

EQ-5D, EuroQol-5 Dimensions questionnaire; HbA1c, glycated haemoglobin; OGTT, oral glucose tolerance test; SAEs, serious adverse events.

#### Sociodemographic characteristics

Participants will be asked to self-report highest education level, employment status and ethnicity. Age will be accessed from the medical records.

#### Physical measurements

Height will be measured using stadiometers, to the nearest 0.1 cm. Weight will be measured to the nearest 0.1 kg using a digital scale (Active Era, BS-03S) at the study visits. For self-weighing at home, participants in the intervention group will be instructed to use their own digital scales or will be given a set by the research team if they do not own a set. They can either text the measurements to the research team or log them manually onto a mobile application (detailed below). At 36 weeks’ gestation, women should be weighed during a routine antenatal appointment at their primary care practice, and digital scales are used for this. If predelivery weight is available, digital scales are also used for this. Blood pressure will be measured in duplicate using a digital blood pressure machine (Omron, M3) after 5 min seated rest, with at least 1 min between each measurements.

#### OGTT and remote glucose and ketone monitoring

Women are asked to attend the study visits after an overnight fast, and to refrain from smoking, vaping, using nicotine replacement therapy or chewed sugary gum for at least 8 hours before. A fasting venous blood sample will be collected for the determination of glucose, HbA1c, insulin concentrations. Participants are provided with a 75 g glucose load (Polycal, Nutricia). Further venous blood samples will be collected at 1-hour and 2-hour postdrink, for the determination of glucose concentrations.

All participants are provided with a Bluetooth-enabled capillary blood glucose and ketone monitoring kit (4SURE Smart Duo, Nipro Diagnostics). The researcher provides a short demonstration and information flyer on how to collect and record the measurements, and advises participants to take a fasting capillary glucose and ketone measurement twice a week. The monitor is connected remotely to a mobile application (Diabetes: M, Sirma Medical Systems), allowing the research team to monitor the readings remotely and escalate concerns to the clinical team. We did not provide cut-offs to participants for fasting capillary glucose and ketone levels, due to lack of level references specific to pregnancy and before GDM diagnosis. Two obstetricians from the study team who are also members of the clinical care team interpreted the measurements on an individual basis and/or based on evidence from non-pregnant populations. The collection of this data during the feasibility study will guide thresholds that can be set for any future trial.

#### Carbohydrate consumption

Participants will complete at baseline (<20 weeks’ gestation) and follow-up (24–28 weeks’ gestation) an online multiple-pass 24-hour recall, validated against interviewer-led multiple-pass recalls in adolescents and adults (Intake 24, Newcastle University).^44 45^ This will be used to primarily assess carbohydrate consumption, but also broader dietary intake. By the time participants enrol in the study (mid-pregnancy), their dietary intake is likely to have stabilised compared with the fluctuations usually observed in the first trimester due to pregnancy symptoms. Intake 24 asks participants to report whether a reporting day was typical with regard to their dietary intake, and this will be taken into account in the analysis.

#### Quality of life

Participants will be asked to fill in a questionnaire about their quality of life, via the European Quality of Life Five Dimension questionnaire and subscale.^46^

### Retention and withdrawal

This study has been designed to run alongside routine antenatal appointments with remote support elements, to minimise the burden associated with attending extra visits. The brief telephone support sessions with a dietitian will act as prompts for the participants to engage with the intervention and self-monitoring. Participants are asked to attend one visit in addition to routine antenatal care. All of the women who take part would be offered an OGTT at 24–28 weeks of pregnancy for the diagnosis of GDM. The 24–28 weeks follow-up study visit and OGTT, replaces the routine care OGTT and the results are shared with the clinical care team. To compensate for the time and inconvenience in taking part, we offer participants financial incentives for their participation.

Each participant will have the right to withdraw from the study at any time, or may be withdrawn at the discretion of the research or clinical care team. Participants will have the right to withdraw their collected data if they wish. Withdrawn eligible and enrolled participants will not be replaced in this feasibility study. We will only replace participants whose baseline OGTT is abnormal, as they will have consented and been randomised before OGTT results become available, but they will have essentially failed the full screening.

### GDM diagnosis

Participants who develop GDM or who are diagnosed with GDM at the 24–28 weeks’ follow-up visit, will be referred to the clinical care team and offered the current standard medical treatment. In line with the NICE guidelines, this includes monitoring of blood glucose (two of the fasting measurements will continue to be used in the study), and diet and physical activity advice for the management of GDM.^36^ More specifically, women with GDM are advised to manage carbohydrate intake, to limit their weight gain until delivery, and are encouraged to do 150 min of moderate intensity activity per week. Women in the intervention group, can choose to continue following the RECORD programme until delivery (at the discretion of the clinical care team). Women in the control group will receive advice to reduce their carbohydrate intake at this stage, and this will be noted. All participants with GDM, will be encouraged to continue monitoring their ketone levels twice a week for the remaining of pregnancy.

### Statistical analysis

Descriptive statistics will be used to report the baseline characteristics of each trial arm. Continuous variables will be reported using mean/median and SD/range, while categorical variables will be reported using frequencies and percentages.

Since this is a feasibility study, the primary outcomes are the main progression criteria which will inform the design of a future RCT, powered to detect a significant difference in the efficacy of the intervention in preventing GDM. Descriptive statistics with 95% CIs will be used to analyse and report the progression criteria. For the analysis of the secondary, process-related and exploratory measures, all data collected up to each time point will be used. Descriptive comparative statistics will be used to analyse and report these measures along with 95% CIs (eg, difference in means or proportions between baseline and follow-up for each group or between the two groups). Data from audiorecorded and transcribed qualitative interviews on acceptability and experience of the intervention by participants will be analysed using thematic analysis and reported descriptively.

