### Recruitment

Participants will be recruited from one maternity care centre in Oxfordshire, UK. The study is expected to run from May 2021 to December 2022. Women attending the dating or nuchal ultrasound scan appointment (typically between 8 and 14 weeks’ gestation) will be approached to take part in the study. Potentially eligible participants will be provided with the participant information sheet, and invited to give their contact details. A member of the research team will contact the women who were interested in taking part to discuss the study and assess self-reported eligibility to participate according to the full inclusion and exclusion criteria as detailed below. Eligible individuals who wish to participate will be booked in for a face-to-face baseline appointment. The aim is to recruit women as early in pregnancy as possible, therefore, we will aim to book the baseline appointment for the trial within 2 weeks after the dating scan. However, we recognise this extra appointment at short notice may be challenging, and during this feasibility trial we will allow women to attend their baseline appointment up to 20 weeks’ gestation. This allows at least a month to practise the dietary changes and assess whether the progression criteria are met. In addition, we will monitor the timing of the baseline appointment to check whether setting a limit at 14 weeks’ gestation for recruitment to any future definitive trial, would be feasible. For those who decline to participate, permission will be sought to record the barriers to participation.

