### Sample size

This feasibility study is not powered to detect a statistically significant difference in clinical effectiveness between the trial arms. Instead, we will test for reductions in carbohydrate intake as preliminary evidence of the adoption of the reduced carbohydrate diet to an extent that is expected to alter health outcomes. The average total carbohydrate intake in women who are not pregnant is about 230 g/day.^34^ We have set the sample size to be able to detect a reduced target intake at 130–150 g, that is, ~140 g of total carbohydrate/day at follow-up, with 95% CI excluding 170 g/day. Progression criteria to a full trial also include adequate retention of participants as a measure of feasibility. We consider that a minimum of 80% of participants need to complete an OGTT at 24–28 weeks’ gestation, similar to previous trials, with 95% CI excluding 70%.^12 16^ Both progression criteria thresholds are satisfied with a sample size of 60 participants allocated in 2:1 ratio, intervention: control. Unequal randomisation allows us to have sufficient participants in the intervention arm for the qualitative study.

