#### Secondary

Change in fasting plasma glucose, 1-hour and 2-hour glucose. (OGTT at baseline and follow-up visit).Change in glycated haemoglobin (HbA1c), fasting plasma insulin and insulin resistance (Homeostatic Model Assessment of Insulin Resistance-HOMA-IR). (Blood samples collected as part of OGTT at baseline and follow-up visit).Proportion of participants who are diagnosed with GDM. (Documentation at baseline and follow-up visit).GWG: weight change from baseline until before delivery. If predelivery weight is not available, we will use weight at 36 weeks’ gestation collected as part of routine practice.Proportion of participants meeting the Institute of Medicine recommendations for GWG.^42^
Dietary intake: total carbohydrate intake (g/day) and total energy intake (MJ/day), percentage of daily total energy intake from carbohydrates. (Dietary composition analysis at baseline and follow-up visit—see details below)Distribution of fasting capillary blood glucose and ketone levels across gestational age from baseline until before delivery.

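### For continuous outcomes measured at both visits, the example analyses name within-arm change or a plain between-arm difference; a baseline-adjusted between-arm difference answers the stated objective better at no data cost

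*Protocol article*

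**What the plan says.** The Statistical analysis section of the protocol article has one rule for secondary, process and exploratory measures: descriptive comparative statistics with 95% CIs. The form is illustrated in a parenthesis that opens with an 'eg': "difference in means or proportions between baseline and follow-up for each group or between the two groups". No covariate is named.

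Several of these outcomes are defined as changes, for instance "Change in fasting plasma glucose, 1-hour and 2-hour glucose. (OGTT at baseline and follow-up visit". HbA1c, fasting insulin and HOMA-IR are defined the same way under Secondary, and blood pressure and quality of life under Exploratory outcomes. Dietary intake is also assessed at both visits. Table 1 and Study procedures show that all participants in both arms have these measurements at baseline and at 24–28 weeks.

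The objectives at the end of the Introduction include assessing the intervention's potential effect on glycaemic markers, diet and quality of life. On the timing of baseline, Recruitment says "we will allow women to attend their baseline appointment up to 20 weeks" of gestation.

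**The concern.** The potential effect of an intervention in a randomised trial is a contrast between arms. The 'or' in the example lets a within-arm change with its own CI stand in place of that contrast. Here such a change carries several things besides the intervention:

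- **Advancing gestation.** Baseline may be as late as 19 weeks and 6 days and follow-up as early as 24 weeks, an interval of about 4 weeks. Baseline soon after a scan at 8 weeks and follow-up at 28 weeks give about 28 − 8 = 20 weeks. Table 1 assumes about 12.
- **Regression to the mean.** Women with baseline fasting glucose of 5.6 mmol/L or above, or 2-hour glucose of 7.8 mmol/L or above, are excluded and replaced (Exclusion criteria; Retention and withdrawal). The OGTT that serves as baseline for the change is therefore cut off from above, and follow-up values tend to drift upward in both arms whatever the treatment.
- **Unequal arms.** With 2:1 allocation, the same average change has a narrower CI in the intervention arm.

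If separate within-arm intervals were all that was reported, a reader could see a change in one arm and none in the other, and take that for an effect.

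**Working it through.** **Inputs.** Total 60, allocated 2:1, so 40 and 20 (Sample size). With 80% retention in each arm, 0.8 × 40 = 32 and 0.8 × 20 = 16. The document gives no correlation r between baseline and follow-up, so r is an assumption and is varied.

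**The plan's own figure.** The article states that "Both progression criteria thresholds are satisfied with a sample size of 60 participants allocated in 2:1 ratio, intervention: control". For 80% retention with a lower limit above 70%, the Wald formula gives n = 1.96² × 0.8 × 0.2 / 0.1² = 61.5, so 62, close to 60; 48/60 has a Wald interval of 69.9% to 90.1%. For carbohydrate ("140 g of total carbohydrate/day at follow-up, with 95% CI excluding 170 g/day") no SD is stated; a half-width of 30 g holds if the SD is at most about 94 g (n = 40) or 83 g (n = 32). Neither calculation uses a between-arm effect, so the point here does not depend on the figure of 60 and would not change it.

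**Precision of the between-arm difference**, in units of the outcome SD, with N = n₁ + n₂:

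- Follow-up means only: SE₀ = √(1/n₁ + 1/n₂). At 40 v 20 this is √0.075 = 0.274.
- Change scores: SE₀ × √(2(1 − r)).
- Baseline-adjusted linear model (ANCOVA): SE₀ × √((1 − r²)(N − 3)/(N − 4)).

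Apart from the degree of freedom, the ANCOVA variance is (1 + r)/2 of the change-score variance and 1 − r² of the follow-up-only variance. The 95% CI half-widths with t quantiles are:

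| Arms | r | Follow-up only | Change | ANCOVA | Narrower than change | Narrower than follow-up only |
|---|---|---|---|---|---|---|
| 40 v 20 | 0.3 | 0.548 | 0.649 | 0.528 | 18.6% | 3.7% |
| 40 v 20 | 0.5 | 0.548 | 0.548 | 0.479 | 12.6% | 12.6% |
| 40 v 20 | 0.7 | 0.548 | 0.425 | 0.395 | 7.0% | 27.9% |
| 32 v 16 | 0.5 | 0.616 | 0.616 | 0.540 | 12.4% | 12.4% |

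Over r = 0.2 to 0.8 the adjusted interval was never the wider one. A low r is plausible for diet, which rests on one 24-hour recall per visit, and that is where change scores do worst.

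**Within-arm reading.** Take the same mean change in both arms, 0.4 of the SD of the change. Then z = 0.4 × √32 = 2.26 in the intervention arm and 0.4 × √16 = 1.60 in control, so only the first exceeds 1.96.

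A simulation (20,000 trials per row, r = 0.5, no true difference between arms, the same drift in both) shows how often the two within-arm 95% CIs disagree about zero:

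| Arms | Common drift (SD) | Exactly one arm excludes zero | Intervention arm alone |
|---|---|---|---|
| 40 v 20 | 0.3 | 48% | 35% |
| 40 v 20 | 0.5 | 45% | 38% |
| 32 v 16 | 0.3 | 43% | 30% |
| 32 v 16 | 0.5 | 52% | 42% |

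A valid 95% CI for the between-arm difference would exclude zero in 100 − 95 = 5% of such trials.

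**The case against.** The strongest reply is that the article fixes very little here. The wording is an example, the analysis is descriptive, and "This feasibility study is not powered to detect a statistically significant difference in clinical effectiveness between the trial arms". Covariates for secondary outcomes commonly belong to the full protocol or an analysis plan, neither of which is shown. This stands as a limit on the weight of the point. It does not remove it, because the published text does name within-arm change with a CI as one acceptable report.

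A reader might infer four stronger things that the document does not support:

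- **That unadjusted or within-arm analysis is mandatory.** The 'eg' makes the list illustrative. The word 'unadjusted' does not appear, and a between-group difference could be an adjusted one.
- **That the listed between-group difference is biased.** Under randomisation a plain difference is unbiased, and the varying interval between visits affects both arms alike. If that contrast is reported, the one-arm reading does not arise; only precision is lost.
- **That the estimates must supply variances for the full trial.** This is not a stated purpose, and Statistical analysis says the future trial would be powered for preventing GDM, a binary outcome.
- **That the z values hold on any scale.** They need the SD of the change. With 0.4 of the outcome SD and r = 0.3, the change SD is √(2 × 0.7) = 1.18 and the z values fall to about 1.91 and 1.35, so neither exceeds 1.96.

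Adjusting for weeks between visits would also be unwise. That interval is settled only at follow-up, after randomisation in an unblinded trial.

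**Conclusion.** The point holds as a modest improvement to the analysis of continuous outcomes measured at both visits in both arms; it is not an error in the plan. Within-arm change does not address the stated objective, and separate within-arm intervals can mislead, more so with 2:1 allocation. The precision gain depends on the assumed correlation: small against follow-up means when r is low, and small against change scores when r is high.

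It does not extend to every secondary outcome. GDM incidence has no usable baseline value, because GDM at baseline is an exclusion. The proportion meeting weight-gain recommendations and the capillary self-monitoring values have no matching baseline measure. Gestational weight gain is already defined as a change from baseline. The progression criteria use the intervention arm's mean intake and overall OGTT completion, so the decision to proceed is untouched.

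**What to change.** Replace the example in Statistical analysis with a statement along these lines: for OGTT glucose, HbA1c, insulin, HOMA-IR, dietary intake, blood pressure and quality of life, the difference between arms at follow-up will be estimated with its 95% CI from a linear model containing arm and the baseline value of the outcome. Gestational age at the baseline visit may be added as a second covariate; weeks between visits should not be. Within-arm changes will be tabulated as description only and not used to judge an effect. Outcomes without a matching baseline value keep a plain between-arm difference with its 95% CI.

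The cost is a change of wording and one degree of freedom per covariate. No extra data are needed and the sample size stays as it is. If an analysis plan already says this, the article's text only needs to agree with it.

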### Qualitative study

A qualitative substudy with participants randomised to the RECORD group will explore participants’ acceptability of the intervention and their overall experience of the study, explore barriers and facilitators to adherence, and identify suggestions that could refine the intervention should it progress to a full RCT.

During the follow-up study visit, a member of the research team will provide participants allocated to the intervention group, with a separate participant information sheet about the qualitative interviews. If participants are happy to have this in-depth discussion about their experiences of the RECORD intervention, a member of the research team will arrange a convenient day and time for a telephone interview. The participants will consent verbally on the phone and the researcher will fill in written consent form. The interviews will last approximately 30 min and all interviews will be audiorecorded and transcribed verbatim. Data will be analysed using thematic analysis. We will conduct interviews with up to 30 participants, or until data saturation is reached.

